### Study population

From January 2017, patients consulting for PAD or AAA in the departments of vascular medicine or surgery in Paris Saint-Joseph Hospital and European Georges Pompidou Hospital will be consecutively included after signed informed consent. Eligible participants, affiliated to the French social security system, are between 55 and 80 years of age at the time of inclusion, have a history of cigarette smoking of at least 30 pack-years, and, if former smokers, have quit within the previous 15 years. Active smoking patients at the time of inclusion in the study must engage in smoking cessation. Peripheral arterial disease is defined according to the following criteria: asymptomatic patients with ankle-brachial pressure index value less than 0.90 or pulse abolition with imaging-documented atherosclerotic vascular disease; symptomatic patients with intermittent claudication or chronic ischemic rest pain with or without tissue loss; acute limb ischemia; presence of AAA, defined as a localized dilation of the aorta of at least 50% in relation to the normal adjacent aorta measured by duplex-ultrasound or CT-scan.; previous arterial revascularization procedure of lower limb (by angioplasty or surgery) or amputation due to PAD.

Exclusion criteria are treatment for, or evidence of, any cancer within 5 years before enrollment, except non-melanoma skin cancer and in situ carcinomas, previous lung resection surgery, acute respiratory tract infection treated with antibiotics in the previous 12 weeks, contraindication to any invasive thoracic procedure, any sign suggestive of prevalent malignancy (unexplained weight loss ≥10% in the previous 12 months, recent hemoptysis…), renal insufficiency (creatinine clearance < 30 ml/mn) not allowing - if appropriate - injection of contrast medium, psychiatric comorbidities or limited life expectancy due to concomitant disease, ECOG Performance Status ≥2.

### Objectives

The primary objective of the study is to determine the diagnostic value of the couple LDCT combined with CTC search for the early detection of smoking associated cancers in a cohort of asymptomatic but high-risk participants presenting with PAD and/or AAA.

The secondary objectives are (1) to describe detected malignancies with this screening strategy and to evaluate patient’s survival, (2) to evaluate the rate of detection of CTCs in the study population, (3) to study the effect of smoking cessation program on patient’s decision to quit smoking, (4) to study the emotional and psychosocial impact of this screening strategy and more specifically related to CTC detection, (5) to assess, adjust and improve communication strategies of health professionals.

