## Methods/design

### Study design

DETECTOR project is a multicentric prospective cohort study, funded by the French National Cancer Institute, the National League against Cancer and the Foundation for Cancer Research, in a collaborative effort of Paris Descartes University associated hospitals and Paris Diderot University. This trial intends to evaluate unenhanced LDCT in combination with the detection of CTC, in the screening of smoking-associated cancers in patients with PAD or AAA as well as the psychological impact of this screening strategy.

After inclusion in the trial, participants will undergo the first round of screening. Participants without prevalent cancer at baseline will undergo two other screening rounds at one-year interval each, combining LDCT and CTC search on a blood sample (Table 1). Participants will be followed for a total of at least 3 years after inclusion.

**Table 1 Tab1:** Study flow chart of examinations

Actions	V0: baseline visit	within 1 m after V0	V0 + 5w	V1(V0 + 1y)	V1 + 5w	V2(V0 + 2y)	V2 + 5w
Information	✓						
Informed consent	✓						
Verification of inclusion and exclusion criteria	✓						
Enrolment	✓						
Psychologist presence^(1)^	✓						
Personal and family medical history^(2)^	✓						
Ongoing treatments	✓			✓		✓	
Socio-demography	✓						
Level of tobacco use	✓						
Screening round: - Blood sampling for CTC detection - LDCT	✓			✓		✓	
Results of the screening round			✓		✓		✓
Psychological counselling^(3)^		✓	✓	✓			
Clinical events since last visit^(2)^				✓		✓	
Adverse events	✓		✓	✓	✓	✓	✓

1: as an observer; 2: focused on cancer and vascular diseases; 3: only for patients who are volunteer to participate at the psychological study

The study sponsor is Paris Saint-Joseph Hospital. The study was registered in the French National Agency for Medicines and Health Products Safety (No N° EUDRACT_ID RCB: 2016-A00657–44) and was approved by the ethics Committee for Persons Protection (Comité de Protection des Personnes Ile de France II, IRB number 1072 and n° initial agreement 2016-08-02). The total duration of the trial is 6 years (inclusion period = 36 months; follow-up = 3 years; ClinicalTrials.gov identifier NCT02849041). Prolonged follow-up of trial participants will be performed each year after the end of the scheduled trial period. The first study participant has been enrolled on January 2017; last patient’s enrollment is expected on December 2019.

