### Inclusion and screening procedures

Clear and detailed information is given to the patient before signed consent is obtained, emphasizing the annual nature of LDCT and blood tests and the possibility of abnormal results that may lead to additional investigations. If active smoker, he (she) is asked to consider smoking cessation and specific advice and supports are provided.

Enrolled participants undergo the first round of screening with LDCT and blood test sampling for CTCs detection. Multidetector scanner is performed with unenhanced acquisitions and low radiation exposure protocol consistent with lung cancer screening protocols [13, 19]. Each LDCT will result in an average effective dose ≤1.5 mSv. Search for CTCs with the ISET technique (Rarecells Diagnostics, Paris, France) is carried out as previously described [20]. Briefly, 10 mL of peripheral blood are collected in buffered EDTA and processed within 1 h of collection. The ISET method is a highly sensitive blood filtration-based approach using a polycarbonate membrane with pores of 8 μm. Most lymphocytes and neutrophils, whose diameter is between 8 and 10 μm, are not retained. Circulating cells, whose diameter is larger than 20 μm, are directly enriched with this technique and their morphology is conserved. Enriched cells are stained with cytological stainings (i.e., May Grunwald Giemsa) providing the possibility of analyzing the nuclear and cytoplasmic characteristics [21, 22]. Patients are considered positive for CTCs based on cytopathological malignant features determined by two experienced cytopathologists (DD, VD) according to previously defined criteria [18, 20, 22].

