## Discussion

The originality of this study in a PAD / AAA population is to involve together, for the screening of cancer in high risk patients, clinicians, radiologists, pathologists as well as psychologists.

Lung cancer is the leading cause of cancer-related death worldwide [28]. This tumor is diagnosed in most cases at an advanced stage with prevalent distant metastases and reduced survival. By considering CTCs detection in a very high-risk selected population for tobacco-induced cancer, we expect to reduce false positive results of conventional imaging and to detect earlier pulmonary but also extra-pulmonary, malignancies when they are still curable.

Smoking cessation is an important factor in reducing mortality. In the NLST study, a cessation of smoking for at least 15 years associated with LDCT screening resulted in a 38% reduction in mortality, much higher than that achieved by the single effect of CT [29]. Participation in a screening study therefore presupposes for active smokers the parallel commitment in a smoking cessation procedure.

Cancer screening procedures have been associated to psychological adverse effects, particularly consequently to false positive results, over-diagnosis and over-treatment. Lung cancer screening causes an increase in anxiety [30], raising concerns about the short and long-term effects of screening on the psychological well-being of patients. By assessing the emotional and psychological impact of screening for cancers due to tobacco, we expect to identify 1/ specific fear, anxiety and psychological distress mechanisms, 2/ coping strategies that may benefit other patients, 3/ stress factors specifically linked to the screening procedure and/or to the medical information delivered to patients. By assessing the patient-doctor communication strategies, we expect to adjust and improve health professional communication skills respectful of patient psychological well-being.

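### Secondary objective 3 asks for the effect of the smoking cessation programme, but every active smoker is exposed to it and no comparator is named, so that effect cannot be identified

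*Protocol article*

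**What the plan says.** Under Objectives, the third secondary aim is "to study the effect of smoking cessation program", with the decision to stop smoking as the outcome. The Study design section states that "DETECTOR project is a multicentric prospective cohort study" and describes no second group.

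Three places say who meets the programme:

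- Study population: "Active smoking patients at the time of inclusion in the study must engage in smoking cessation".
- Inclusion and screening procedures: "If active smoker, he (she) is asked to consider smoking cessation and specific advice and supports are provided".
- Discussion: "Participation in a screening study therefore presupposes for active smokers the parallel commitment in a smoking cessation procedure".

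The statistical section assigns the secondary criteria the methods of the primary endpoint, which are single-group proportions with a binomial interval. It also lists standard two-group tests without saying which groups they would compare. In Table 1 the tobacco-use row is ticked at the baseline visit only. The data-collection section lists smoking habits but ties them to no visit.

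**The concern.** An effect is a contrast between what happened with the programme and what would have happened without it. The design observes only the first. The same smokers are also under vascular care, are scanned and blood-tested each year, and may go on to a cancer work-up. If commitment to stopping is a condition of entry, they have also been selected for willingness to quit. Each of these could change quitting without any contribution from the programme.

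What is at stake is the conclusion the study may draw on this objective. With the present wording, a quit proportion at one or two years could be presented, or read by others, as evidence about the programme.

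**Working it through.** **1. The article's only planning figure.** The sample size is 30 cancers / 0.10 prevalence = 300 participants, which reproduces. It concerns cancer detection. Nothing is stated for objective 3: no number of active smokers, no expected quit rate and no reference rate. The rest is therefore a reading of the design, followed by an illustration.

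**2. Is there a contrast anywhere?**

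| Where a contrast could come from | What the article gives |
|---|---|
| A randomised or parallel group | None; one cohort |
| Active smokers not offered the programme | None; all are asked and supported |
| A delayed, historical or external reference | None named |
| The two-group tests in the statistical section | Groups not named; no group of active smokers is without the programme |
| The methods assigned to secondary criteria | Single-group proportions |

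The eligibility text makes engagement compulsory, while the procedures text only asks the smoker to consider stopping. The two should be reconciled, but this point holds under either. On the first reading every active smoker has committed. On the second, uptake may vary, but the offer does not. Smokers who take up the support and those who decline it differ in motivation, so a comparison by uptake would be confounded.

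**3. What a quit proportion can and cannot say.** Let q1 be the proportion who quit in the cohort and q0 the proportion of the same smokers who would have quit under the same care and screening without the programme. The effect is q1 − q0. The study can estimate q1 only.

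**4. Illustration on assumed figures.** Assume 30%, 50% or 70% of the 300 are active smokers and q1 = 20%. The 95% interval is q1 ± 1.96 × √(q1(1 − q1)/m).

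| Active smokers m | Standard error | 95% CI for q1 |
|---|---|---|
| 300 × 0.3 = 90 | √(0.16/90) = 0.042 | 11.7% to 28.3% |
| 300 × 0.5 = 150 | √(0.16/150) = 0.033 | 13.6% to 26.4% |
| 300 × 0.7 = 210 | √(0.16/210) = 0.028 | 14.6% to 25.4% |

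The effect, for assumed values of q0:

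| q0 | q1 − q0 |
|---|---|
| 0% | 20 points |
| 5% | 15 points |
| 10% | 10 points |
| 20% | 0 points |

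The first table narrows as m grows. The second does not change with m, because q0 is not estimated at any sample size. That conclusion does not depend on the assumed figures.

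**5. Can even q1 be computed?** Not from the schedule as printed, since Table 1 places tobacco use at V0 only. This is a separate gap. Filling it would make q1 available but would leave q0 unknown.

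**The case against.** The best reply is that the point rests on one noun in a one-line secondary objective. The article is condensed. The content of the programme, the definition of quitting and any external reference rate may be in the full protocol or the analysis plan. The methods named for secondary criteria are already descriptive when applied to quitting.

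Part of this stands. A reader might infer that quitting will be credited to the programme. The article does not say so: it writes no estimand, analysis or conclusion for this objective, and the Discussion makes no claim that the programme works. A reader might also infer that the bias must favour the programme. Crediting every quitter to it would indeed overstate the effect, by q0, but the article does not plan that. Against any reference rate the sign is open: a reassuring scan could discourage quitting and a worrying one could prompt it, and nothing in the documents settles the net direction. The figures in the illustration are assumptions and do not measure harm.

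What does not stand is the appeal to an analysis plan. It can choose a model or cite an outside rate, but it cannot create a concurrent group of smokers without the programme. An outside rate would still not separate the programme from screening and vascular care. Descriptive methods do not cure the wording either; they show that the planned analysis does not answer the stated question.

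**Conclusion.** The point holds in this limited form. Objective 3 asks for an effect that the described design cannot identify, because all active smokers are exposed and no comparator is named. A quit proportion could be misread as that effect. The size and direction of any resulting bias cannot be determined from the documents; the 0 to 20 point range above depends wholly on an assumed 20% quit rate and an assumed background of 0 to 20%.

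The consequence is confined to one of five secondary objectives. The primary diagnostic-accuracy objective, the sample size and the screening pathway are unaffected. The change is still worth making, because it corrects what the study may conclude at very little cost.

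**What to change.** Three linked edits:

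1. Reword objective 3 as: *to describe the proportion of participants actively smoking at inclusion who have stopped at V1 and V2*.
2. Add to the statistical section that this proportion is reported with a binomial 95% CI among baseline active smokers and is not interpreted as an effect of the programme.
3. Tick the tobacco-use row of Table 1 at V1 and V2. Without this, the reworded objective has no scheduled data.

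The cost is giving up a causal claim on a secondary objective and asking one extra question at visits already scheduled. No extra participants or visits are needed.

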### Inclusion and screening procedures

Clear and detailed information is given to the patient before signed consent is obtained, emphasizing the annual nature of LDCT and blood tests and the possibility of abnormal results that may lead to additional investigations. If active smoker, he (she) is asked to consider smoking cessation and specific advice and supports are provided.

Enrolled participants undergo the first round of screening with LDCT and blood test sampling for CTCs detection. Multidetector scanner is performed with unenhanced acquisitions and low radiation exposure protocol consistent with lung cancer screening protocols [13, 19]. Each LDCT will result in an average effective dose ≤1.5 mSv. Search for CTCs with the ISET technique (Rarecells Diagnostics, Paris, France) is carried out as previously described [20]. Briefly, 10 mL of peripheral blood are collected in buffered EDTA and processed within 1 h of collection. The ISET method is a highly sensitive blood filtration-based approach using a polycarbonate membrane with pores of 8 μm. Most lymphocytes and neutrophils, whose diameter is between 8 and 10 μm, are not retained. Circulating cells, whose diameter is larger than 20 μm, are directly enriched with this technique and their morphology is conserved. Enriched cells are stained with cytological stainings (i.e., May Grunwald Giemsa) providing the possibility of analyzing the nuclear and cytoplasmic characteristics [21, 22]. Patients are considered positive for CTCs based on cytopathological malignant features determined by two experienced cytopathologists (DD, VD) according to previously defined criteria [18, 20, 22].

### Management of incidental findings

First-line screening incidental findings and adapted screening strategy are displayed in Table 2. In case of negative LDCT or incidental lung nodule(s) with a volume < 50 mm^3^ and absence of CTCs, this screening strategy will be repeated once a year for a total of 3 consecutive rounds. Participants will be excluded from further screening when diagnosed with lung cancer or extra-pulmonary malignancy. In case of incidental lung nodule(s) with a volume > 500 mm^3^, in the presence or absence of CTCs, a specific multidisciplinary team meeting will discuss diagnostic and pre-therapeutic evaluation for lung cancer [23]. In case of incidental lung nodule(s) with a volume between 50 and 500 mm^3^ and presence of CTCs, diagnostic and pre-therapeutic evaluation for lung cancer will also be performed. In the absence of CTCs, volume doubling time - evaluated through a second LDCT performed three months later - will be taken into consideration for adapted diagnostic management. In case of negative LDCT or incidental lung nodule(s) with a volume < 50 mm^3^, and presence of CTCs, a contrast enhanced whole-body scanner and PET/CT associated with clinical head and neck examination and cytological examination of the urine will be performed for extra-pulmonary malignancy screening and management (Fig. 1).

**Table 2 Tab2:** First-line screening incidental findings and adapted screening strategy

Low –dose chest CT and search for CTCs	No incidental lung nodule or nodule(s) <50mm^3^	Incidental lung nodule(s) with volume between 50 and 500mm^3^	Nodule(s) >500mm^3^
No CTC	Next screening round at one year	Measure of volume doubling time at low-dose chest CT 3 months later	Diagnostic and pretherapeutic evaluation
Presence of CTC	Contrast enhanced whole-body scanner and PET/CT examination of the head and neck cytological examination of the urine	Diagnostic and pretherapeutic evaluation	Diagnostic and pretherapeutic evaluation

*CTC: circulating tumor cells; PET/CT: Positron emission tomography-computed tomography*

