### Statistical analysis and sample size

Data will be analyzed using SAS and R software. Alpha level for statistical significance (p) will be set at less than 5%. Characteristics of the study population will be described as mean plus or minus standard deviation for continuous variables with a normal distribution and as median [interquartile range] for skewness distribution. Categorical variables will be described as numbers and proportions. Student’s t-test or nonparametric Wilcoxon test will be used to compare quantitative parameters between different groups of patients and Chi2 test or Fischer test for qualitative parameters.

The primary outcome will focus on the sensibility and specificity of the screening strategy associating detection of CTCs and LDCT. Statistical analysis is in accordance with the STARD (Standards for Reporting of Diagnostic Accuracy Studies) guidelines [24]. To meet the primary objective, sensitivity will be estimated by dividing the number of patients diagnosed by the CTC method by the number of patients with lung cancer confirmed by the reference technique, i.e. LDCT. The results will be expressed with a binomial proportion 95% confidence interval. Specificity will be estimated by dividing the number of patients diagnosed with CTC as cancer-free with the number of patients without lung cancer. Secondary evaluation criteria will be analyzed using the same statistical methods as those used for the primary endpoint.

Assuming 10% prevalence of smoking-associated cancer in the studied population [8], if we aim to study a total of at least 30 detected cancers, including baseline and repeat screening rounds, we need to enroll a total of at least 300 participants.

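### The index tests decide who is worked up and no rule counts cancers found later, so the LDCT + CTC pair's sensitivity for smoking-associated cancer is biased upwards

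*Protocol article*

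**What the plan says.** - **Target.** The Objectives section sets out to "determine the diagnostic value of the couple LDCT combined with CTC search for the early detection of smoking associated cancers". This covers all smoking-associated cancers and both tests together.
- **Work-up.** Under Management of incidental findings and in Table 2, the two test results determine what happens next. With a negative LDCT or nodules below 50 mm³, CTC-positive participants get whole-body imaging, PET/CT, a head and neck examination and urine cytology. For CTC-negative participants the text provides: "absence of CTCs, this screening strategy will be repeated once a year for a total of 3 consecutive rounds". With nodules of 50–500 mm³, CTC status decides between diagnostic evaluation and a repeat LDCT at three months. Nodules above 500 mm³ are evaluated whatever the CTC result.
- **Estimator.** Statistical analysis and sample size divides the patients diagnosed by CTC by the lung cancers that LDCT, named as the reference technique, has confirmed. The section states: "Statistical analysis is in accordance with the STARD (Standards for Reporting of Diagnostic Accuracy Studies) guidelines". It does not say how a cancer that surfaces after a negative round is classified.
- **Follow-up.** Study design says: "Participants will be followed for a total of at least 3 years after inclusion". It adds yearly follow-up after the scheduled period. In Table 1 the row "Clinical events since last visit", footnoted as covering cancer and vascular disease, is ticked at V1 and V2 only. The last column is V2 + 5 weeks.

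**The concern.** This is partial and differential verification driven by the index tests. Extra-pulmonary cancer is actively sought only after a positive CTC result on a negative LDCT. A CTC-negative participant with, say, a bladder or a head and neck cancer meets only the same two tests again, one of which images the chest alone. The cancer is seen only if a later CTC result turns positive or the patient presents clinically.

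The denominator adds to this. A cancer that LDCT misses cannot be confirmed by LDCT, so it cannot enter the calculation, and extra-pulmonary cancers are outside it altogether. Since no rule brings later cancers back to the round that missed them, the primary result cannot show how many cancers the strategy fails to find. For a screening strategy, that is the question sensitivity should answer.

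**Working it through.** **1. The plan's own figure.** Three inputs come from Statistical analysis and sample size. The prevalence is given as "Assuming 10% prevalence of smoking-associated cancer in the studied population". The target number of cancers is worded as "if we aim to study a total of at least 30 detected cancers, including baseline and repeat screening rounds". The resulting minimum enrolment is 300. 30 / 0.10 = 300, which reproduces exactly. The 30 is described as detected cancers, while 10% is a prevalence. The two agree only if every cancer present is detected.

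**2. How a cancer can be verified, by test pattern (Table 2).**

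| LDCT | CTC | Protocol action | Extra-pulmonary search |
|---|---|---|---|
| negative or < 50 mm³ | negative | next annual round | none |
| negative or < 50 mm³ | positive | whole-body imaging, PET/CT, head and neck, urine | yes |
| 50–500 mm³ | negative | LDCT at 3 months | none stated |
| 50–500 mm³ | positive | diagnostic evaluation | none stated beyond the lung cancer evaluation |
| > 500 mm³ | either | diagnostic evaluation | none stated beyond the lung cancer evaluation |

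**3. Effect on the pair's sensitivity.** Let Se be the pair's true sensitivity and v the share of the cancers it misses that are later found and counted. Neither is in the documents; both are assumptions, with Se from 60% to 90% and v from 0 to 1.

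Apparent sensitivity = Se / (Se + (1 − Se) × v)

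For Se = 70% and v = 0.5: 0.70 / (0.70 + 0.30 × 0.5) = 0.70 / 0.85 = 82.4%. In counts, with 30 true cancers (300 × 0.10) of which 21 are found: 21/21 = 100%, 21/25.5 = 82%, 21/30 = 70%.

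| True Se | v = 0 | 0.25 | 0.5 | 0.75 | 1 |
|---|---|---|---|---|---|
| 60% | 100% | 85.7% | 75.0% | 66.7% | 60.0% |
| 70% | 100% | 90.3% | 82.4% | 75.7% | 70.0% |
| 80% | 100% | 94.1% | 88.9% | 84.2% | 80.0% |
| 90% | 100% | 97.3% | 94.7% | 92.3% | 90.0% |

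The estimate is too high whenever v < 1 and reaches 100% only at v = 0.

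**4. The interval does not warn the reader.** Exact binomial 95% intervals, 30 true cancers:

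| True Se | v = 0 | v = 0.5 | v = 1 |
|---|---|---|---|
| 80% | 24/24: 85.8–100% | 24/27: 70.8–97.6% | 24/30: 61.4–92.3% |
| 60% | 18/18: 81.5–100% | 18/24: 53.3–90.2% | 18/30: 40.6–77.3% |

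At v = 0 the interval excludes the true value in both rows.

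**5. If 30 is the number detected.** Missed cancers = 30/Se − 30, which is 20 at Se = 60% and about 3 at Se = 90%.

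**6. Specificity hardly moves.** Take an assumed 243/270 = 90.0%. Counting 3 missed cancers as true negatives gives 246/273 = 90.1%; counting 12 gives 255/282 = 90.4%. The damage is to sensitivity.

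**7. Timeline in Table 1.** V2 + 5 weeks is 104 + 5 = 109 weeks, or about 2.1 years; three years is 156 weeks. Round 1 has a 12-month outcome at V1 and round 2 has one at V2. Round 3 would have its outcome at V0 + 3 years, where the table has no column.

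**The case against.** The strongest reply is that double-negatives are followed. Both tests are repeated at V1 and V2, cancer events are recorded at both visits, and Study design promises at least 3 years and then yearly follow-up. A reader might infer from Table 2 that double-negatives are never verified; these provisions rule that out, and v = 0 is unlikely. Table 1 is titled as a chart of examinations, so the missing year-3 column may be only a matter of display that the full protocol resolves. All of this stands. It shows that missed cancers can surface, not that they are counted as false negatives.

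A second reply is that the arithmetic above is for the pair, whereas the formula in the statistical section puts CTC alone over LDCT-confirmed lung cancers. That is correct. In the written ratio, a CTC-negative cancer confirmed by LDCT is a false negative, so the ratio is not driven to 100%. But it is not the quantity named in the Objectives, and it still leaves out every cancer that LDCT misses. If LDCT were kept as the reference for the pair, sensitivity would be 100% by construction, because LDCT is part of the pair.

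A third reply is that the nodule pathway mainly changes timing: CTC-negative nodules of 50–500 mm³ do get a repeat LDCT. This is also fair. The verification gap lies mainly with extra-pulmonary cancer and with double-negatives.

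Finally, leaving detail to a full protocol or analysis plan is normal for an article. That does not cover the reference standard, which the article states and fixes as LDCT.

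**Conclusion.** The point holds. The index tests determine verification, the stated denominator is confined to LDCT-confirmed lung cancers, and no rule assigns later cancers to the round that missed them. Followed as written, the plan gives a wrong primary result for its stated objective, and the pair's sensitivity is biased upwards.

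The size cannot be derived from the documents, because neither the true sensitivity nor the share of missed cancers that is captured is given. Under the assumptions shown, a true 70% reads as 82% at half capture and a true 60% as 75%. A reader might take 100% as the expected result; it is only the zero-capture limit for the pair. A reader might also suppose that participants who die or are lost are counted as cancer-free. No section says so, and their handling may properly sit in an analysis plan that is not shown.

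The mismatch between Table 1 and the promised 3 years is real but secondary: the table shows no outcome contact for round 3, while the text implies one.

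**What to change.** In Statistical analysis and sample size, replace the LDCT-only reference with one composite reference applied to every participant, for example:

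> For each round, a participant has the target condition if a smoking-associated cancer is confirmed, from any source, during the round or within 12 months after it, up to and including the next annual round. A participant is free of it if cancer-free at 12 months. A cancer that surfaces in this window after a negative round, whether between rounds or at the next round, is a false negative of that round.

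Apply this reference to the LDCT + CTC pair, the strategy named in the Objectives. In Table 1, add the promised V0 + 3 years contact, recording cancer events and vital status, so that round 3 has the same 12-month window and the table agrees with the text.

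The cost is one contact per participant, which the text already implies, and analysis wording; no imaging or procedure is added. Sensitivity will look less favourable, partly because some cancers that arise after a round will count against it. Round 3 will still be verified less closely than rounds 1 and 2, since no screening round follows it, and the report should say so.
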